**3.3 Study Population**

Participants will be recruited through BluedHealth, the main online PrEP sales platform in China, operated by Beijing Blued Health Management Co., Ltd. The study population will consist of individuals in China who purchase PrEP online.

**Inclusion criteria:**

- Age ≥18 years.
- Purchased PrEP online via BluedHealth.
- Eligible for PrEP use according to national guidelines (e.g., HIV-negative, no contraindications to PrEP such as significant renal impairment, at high risk of acquiring HIV such as having condomless anal sex, having a HIV-positive partner whose viral load is not confirmed as suppressed, have been newly diagnosed with a sexually transmitted infection, inject drugs and share equipment, or have repeatedly used post-exposure prophylaxis).
- Planning to use PrEP over the next six months.
- Willing to provide informed consent.

**Exclusion criteria:**

- Communication barriers or reading disabilities reported by recruiters or researchers (e.g., being unable to read the invitation message or difficult to communicate with the recruiters).

**3.4 Recruitment Procedure**

Recruitment will be conducted in collaboration with BluedHealth. Staff from BluedHealth will distribute recruitment materials (texts and posters) containing a unique identification key and contact details. The unique keys will be generated using a four-digit code plus a letter (e.g., 1001c, 1002d), ensuring each participant can be individually tracked.

The first round of recruitment will target individuals who purchased PrEP within one month prior to study initiation. If fewer than 650 participants are enrolled within two weeks, subsequent rounds will expand eligibility to those who purchased PrEP within the past two or three months, until the target sample size is reached (ideally within 30 days).

Recruiters will contact eligible clients through BluedHealth customer service channels or directly at the time of PrEP purchase, inviting them to join the study. Interested individuals will scan a WeChat QR code to connect with study investigators. Prospective participants must include their unique key when adding the investigator to confirm identity. Investigators will verify inclusion/exclusion criteria, obtain informed consent, and finalize enrollment.

A reminder mechanism will be implemented: after receiving the QR code, potential participants will receive up to two reminders within 48 hours. If they do not respond, the key will be invalidated. Each participant’s unique key will serve as their identifier throughout the study(figure 1).

[figure not shown]

Figure 1 Flowchart of the study procedure

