**3.2 Sample Size Calculation**

The required sample size is calculated using Cochran’s formula for estimating a single population proportion, incorporating finite population correction and a design effect adjustment, as shown in Equation (1). Based on previous studies, we assumed an optimal adherence prevalence of 60%, a two-sided significance level of α = 0.05, and a desired precision (margin of error) of 5%.

A design effect (deff) is included to account for potential clustering introduced by the recruitment workflow, since participants will be conveniently recruited by the designated recruiters through the same platform channels may share unobserved similarities. Following the standard formula deff = 1 + (m – 1) × ICC, we assumed an average cluster size of approximately 11 participants per recruiter and a small intraclass correlation coefficient (ICC) of 0.01. This yielded deff ≈ 1.1, which is applied as a conservative adjustment [7,8].

In addition, a 15% anticipated loss to follow-up is included. The final minimum required sample size is calculated to be 424 participants using PASS software.

n = deff × [N p̂ q̂] / [(d² / 1.96²)(N – 1) + p̂ q̂] (1)

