**3.5 Baseline and Follow-up Visits**

Following enrollment, participants will complete a baseline questionnaire delivered through Wenjuanxing (an online survey platform) via WeChat. The questionnaire covers socio-demographics, PrEP regimen, adherence, psychosocial measures, and sexual behaviors. Completion time is approximately 10-15 minutes. Data will undergo quality checks, and participants passing these checks will receive a 50 CNY BluedHealth voucher, valid for three months.

Follow-up assessments will occur at 1, 3, and 6 months after baseline. Survey links will be delivered individually via WeChat, and participants will again receive vouchers upon quality-verified completion.

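### Recruits differ in time since purchase and in first or repeat status, but no listed measure or model term captures this, so wave and factor estimates mix stages of use

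*Protocol*

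**What the plan says.** - **Who qualifies.** The inclusion criterion is "Purchased PrEP online via BluedHealth". It sets no window and does not require a first purchase. Everyone must also intend to keep using PrEP for the coming six months.
- **When they bought.** Section 3.4 opens with "The first round of recruitment will target individuals who purchased PrEP within one month prior to study initiation". The same section lets recruiters approach clients through customer service "or directly at the time of PrEP purchase, inviting them to join the study". The wider window is conditional: "If fewer than 650 participants are enrolled within two weeks", then "subsequent rounds will expand eligibility to those who purchased PrEP within the past two or three months, until the target sample size is reached". The date from which those two or three months are counted is not given.
- **How time is measured.** Section 3.5: "Follow-up assessments will occur at 1, 3, and 6 months after baseline".
- **What enters the outcome.** For event-driven (ED) users, Section 3.6 builds past-one-month and past-three-month adherence from baseline as well as follow-up answers. In Section 3.8, Model 1 pools baseline with months 3 and 6, and Model 2 pools baseline with all follow-up visits.
- **What is measured and modelled.** Section 3.6 lists demographics, sexual behaviour, dosing knowledge, stigma, self-efficacy, depressive symptoms and resilience. Neither that list nor the models in Section 3.8 name time since purchase or first dose, first versus repeat purchase, or recruitment round.
- **Size.** Section 3.2: "The final minimum required sample size is calculated to be 424 participants".

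**The concern.** A person approached at checkout and a person who bought three months ago both have a month-1, month-3 and month-6 visit, but those visits fall at different stages of use. If adherence changes with experience, the prevalence at a wave depends partly on how many recruitment rounds were needed. Factors that may also change with experience, such as self-efficacy or stigma, can be confounded by time since purchase.

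Two mechanisms could act:
- **Selection.** Earlier buyers who have already given up are screened out by the intention-to-continue criterion. Someone at the point of sale has had no time to give up.
- **Recall.** The baseline questions look back one and three months. For a recent first-time buyer, part or all of that period lies before the purchase.

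At stake are the reading of the wave prevalences and of the odds ratios, which together form the primary objective. A later analysis plan cannot repair this if purchase history is not collected at baseline.

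**Working it through.** **1. The plan's own figure.** Equation (1) in Section 3.2 with p = 0.60, d = 0.05, design effect 1.1 and 15% loss. N is not stated. Section 1 reports just over 3,000 sales a month, so N = 3,000 is an assumption.

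- n = 1.1 × 3,000 × 0.24 / [(0.0025/3.8416) × 2,999 + 0.24] = 792 / 2.1917 = 361.4; 361.4 / 0.85 = 425.1. This agrees closely with 424, which is matched exactly at N of about 2,930.
- Infinite population: 405.7 / 0.85 = 477, which does not match.
- N = 9,000 (three months of sales, assuming each sale is a different buyer): 389.7 / 0.85 = 459.

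The stated minimum therefore fits a population of about one month of buyers. A three-month population raises it by 8%, still well below 650.

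**2. Time since qualifying purchase at each visit** (months; recruitment from point of sale to three months back)

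| Visit | Window counted from enrolment | Upper end if counted from study initiation, plus 30 days of recruitment |
|---|---|---|
| Baseline | 0 to 3 | 4 |
| Month 1 | 1 to 4 | 5 |
| Month 3 | 3 to 6 | 7 |
| Month 6 | 6 to 9 | 10 |

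The month-1 visit of a three-month-old buyer (month 4) comes later after purchase than the month-3 visit of a point-of-sale recruit (month 3).

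**3. Baseline recall window for a first-time ED buyer.** With t months since purchase (t ≤ 3), the share of the three-month window before purchase is (3 − t)/3.

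| t | Three-month window before purchase | One-month window before purchase |
|---|---|---|
| 0 | 3/3 | all |
| 1 | 2/3 | none |
| 2 | 1/3 | none |
| 3 | 0 | none |

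ED adherence requires PrEP at every encounter in the window. A first-time buyer at t = 1 who had sex in the two earlier months, and had no other source of PrEP, cannot be classed adherent at baseline whatever happened after purchase. A first-time buyer at t = 3 can. A buyer who has not started is set to missing. A repeat buyer is not affected in this way. At month 3 the three-month window starts at baseline, so it lies after purchase for everyone. The problem is therefore specific to baseline, which Models 1 and 2 pool with the later visits.

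**4. Selection among earlier buyers.** The protocol gives no retention figures, so this is an illustration. Let 60% be the adherence of new buyers (the planning value), s1 and s0 the retention of adherent and non-adherent buyers up to enrolment, and f the share of earlier buyers in the sample.

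Earlier buyers: p_e = 0.6·s1 / (0.6·s1 + 0.4·s0). Pooled: (1 − f) × 0.60 + f × p_e.

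| s1, s0 | p_e | f = 25% | f = 50% | f = 67% |
|---|---|---|---|---|
| 0.9, 0.7 | 65.9% | 61.5% | 62.9% | 63.9% |
| 0.9, 0.5 | 73.0% | 63.2% | 66.5% | 68.7% |
| 0.8, 0.8 | 60.0% | 60.0% | 60.0% | 60.0% |
| 0.7, 0.9 | 53.8% | 58.5% | 56.9% | 55.9% |

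The pooled shift runs from about −4 to +9 points. Its sign depends on whether s1 exceeds s0.

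**The case against.** **A mixed cohort is legitimate.** The objective concerns adherence among people who buy PrEP online, not among initiators followed from first purchase, and the visits are openly defined from baseline. This stands. The mix itself is not the fault; the fault is that it is neither defined nor captured.

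**Purchase date is not time on PrEP.** A point-of-sale recruit may be a long-term repeat buyer, and someone who bought three months ago may never have started. This also stands. It means the mixing exists even without the wider window, which is why first or repeat status is needed as well as the date.

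**The covariate list may be incomplete.** Section 3.8 does not enumerate its covariates, and Section 3.6 relies on an initiation question that it does not itself list. The absence is therefore one of listed items only. But Section 3.6 sets out the measures at length, and purchase history has to be collected at baseline.

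**Selection bias is already acknowledged.** The limitations attribute it to convenience sampling and do not mention time since purchase.

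Three stronger readings are tempting and not supported:
- *Adherence is inflated.* This requires better retention among adherent buyers, for which the protocol gives no figure. Equal retention gives no shift and the reverse gives a lower value.
- *The shift far exceeds the 5-point margin.* If 20% stop and 30% of them are adherent, those who remain show (0.60 − 0.06)/0.80 = 67.5%. That 7.5-point shift applies to late-round recruits only; pooled, it is 1.9 points at a 25% share and 3.8 at 50%.
- *650 contradicts 424.* The protocol calls 424 a minimum, and recruiting above a minimum is ordinary.

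**Conclusion.** The point holds as a gap in definition and measurement with possible bias or confounding. It is not a demonstrated overestimate of adherence. The documents establish the spread in time since purchase (0 to about 3 months at baseline, or about 4 if the window counts from study initiation), the eligibility of repeat buyers, the baseline time origin, and the lack of any listed variable that separates these groups. The upper end applies only if enrolment is short of 650 after two weeks.

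The baseline wave is most exposed. For recent first-time ED buyers its recall window reaches back before purchase, by up to the whole window, so baseline adherence depends partly on when people were recruited. This needs no retention assumption, but it does assume sex in the pre-purchase period and no other PrEP source. For selection, −4 to +9 points is an illustration resting entirely on assumed retention and mix. The net direction cannot be determined from the protocol. This is worth correcting before baseline data are collected.

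**What to change.** 1. In Sections 3.3 and 3.4, count the purchase window back from each person's enrolment date and reconcile it with point-of-sale recruitment, which lies outside a window ending at study initiation.
2. Record for each participant the index purchase date, whether it is a first or repeat purchase (or prior PrEP use), and the recruitment round.
3. Add time since purchase and first or repeat status as covariates in all models.
4. Report adherence at each wave for new and prior users separately.
5. Add a sensitivity analysis that leaves out baseline records whose recall window starts before first purchase or initiation.
6. State that 650 is the enrolment target and 424 the minimum.

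The trigger for widening should not be lowered to 424. ED and daily users are reported separately, and 424 × 0.85 is about 360 completers. Split equally (an assumption), 180 per regimen gives 1.96 × √(0.24/180) = ±7.2 points. With 650, about 552 completers or 276 per regimen give 1.96 × √(0.24/276) = ±5.8 points. Both ignore the design effect and the finite population correction.

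The cost is a few baseline fields, two further model terms and wider intervals in the stratified estimates. No extra participants are needed.

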**3.5 Baseline and Follow-up Visits**

Following enrollment, participants will complete a baseline questionnaire delivered through Wenjuanxing (an online survey platform) via WeChat. The questionnaire covers socio-demographics, PrEP regimen, adherence, psychosocial measures, and sexual behaviors. Completion time is approximately 10-15 minutes. Data will undergo quality checks, and participants passing these checks will receive a 50 CNY BluedHealth voucher, valid for three months.

Follow-up assessments will occur at 1, 3, and 6 months after baseline. Survey links will be delivered individually via WeChat, and participants will again receive vouchers upon quality-verified completion.

**3.6 Questionnaires and Measures**

The baseline and follow-up survey questionnaires are developed based on the study aims, previous literature, and expert consultation. The draft questionnaires will be pilot tested among 5-10 e-consumers of PrEP, and be modified and finalized based on their comments and suggestion.

**Primary Outcome**

The primary outcome of this study is PrEP adherence, assessed separately for daily and event-driven (ED) regimen users at each follow-up visit (1, 3, and 6 months after baseline).

- **ED users:** Adherence to ED regimen is assessed by four items. First, the participants are asked whether they had engaged in sexual activity in the past one and three months, respectively (the 1-month follow-up survey only asked this question for the past one month). Those who answer “no” or reported to have never initiated PrEP in a previous question were treated as missing data for PrEP adherence. Those who answer “yes” are then asked if they had taken PrEP for each sexual encounter in the corresponding time period, including those with both primary (e.g., main or long-term partners) and non-primary (e.g., casual or commercial partners) sexual partners (1 = every time, 2 = sometimes, and 3 = never). The participants who choose “every time” or “sometimes” are subsequently asked three adherence questions based on the ‘2-1-1’ dosing guideline: (i) whether (yes or no) they took two pills of PrEP 2 to 24 hours before the sexual activity for each medication (timepoint A); (ii) whether they took one pill 24 hours after the first dose for each medication (timepoint B); and (iii) whether they took another pill 48 hours after the first dose for each medication (timepoint C). The participants who reported to take PrEP for each sexual encounter and chose “yes” to all three adherence questions are classified as “being adherent,” otherwise, they would be classified as “non-adherent.” Lastly, three binary outcome variables are constructed: past 1-month adherence based on baseline and all follow-up data, past 3-month adherence based on baseline and 3- and 6-months follow-up data, and consistent adherence based on 3- and 6-months follow-up data (defined as having optimal past 3-month adherence at both 3- and 6-month follow-up surveys).
- **Daily users:** Adherence to daily PrEP regimen is assessed with a single item: “In the past month, have you ever failed to take PrEP on time and in a correct dosage? (yes/no).” Participants who answer “no” are classified as “adherent,” and those who chose “yes” are categorized as “non-adherent”

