To address this gap, the Real-world E-Consumer Cohort of pre-exposure prophylaxis (RECOPE) is established as the first prospective cohort study targeting individuals purchasing PrEP online in China.

1. **Study Objective:**
2. **Primary Objective**

To evaluate medication adherence among real-world e-consumers of PrEP in China, with a focus on both event-driven (ED) and daily regimens, over baseline and three follow-up visits (1, 3, and 6 months), to identify socio-demogrphic and psycho-behavioral factors associated with PrEP adherence, including self-efficacy, PrEP-related stigma, depressive symptoms, and sexual behaviors (e.g., number of partners, chemsex, condom use, sexual role), and to provide evidence to inform interventions that optimize real-world PrEP effectiveness.

1. **Secondary Objectives**

- To assess the utilization of other HIV-related services (e.g., willingness to use long-acting injectable PrEP, HIV testing behavior)
- To evaluated the factors associated with the utilization of other HIV-related services.

1. **Study Design and Methodology**

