**Regression Analyses**

**Event-driven (ED) users:** Three regression models will be fitted:

- Model 1: A univariable and multivariable generalized linear mixed model (GLMM) with a logit link and random intercept to evaluate factors associated with past three-month adherence using data from baseline, 3-month, and 6-month visits. In the multivariable GLMM, all the exposure variables of interest will be involved.
- Model 2: A univariable and multivariable GLMM with the same structure to evaluate factors associated with past one-month adherence using data from baseline and all follow-up visits.
- Model 3: A logistic regression model for consistent adherence, defined using data from the 3- and 6-month follow-ups, with baseline socio-demographics and averaged time-varying covariates included as independent variables.

**Daily users:** Regression analysis is planned only for past one-month adherence (Model 2), using a GLMM with the same structure as for ED users.

All models will include fixed effects for exposure variables of interest. Univariable GLMMs will be fitted first to estimate crude odds ratios (ORs) and 95% confidence intervals (CIs) for each covariate. Multivariable GLMMs will then be fitted including all pre-specified, theory-driven covariates—regardless of their univariable associations—to estimate independent effects while adjusting for potential confounding.

Missing data will be handled under a complete case framework. Specifically, missing data are expected to arise primarily from loss to follow-up. No imputation will be performed. GLMM models inherently allow for unbalanced data across repeated measures, and participants with incomplete follow-up will contribute all available observations. Attrition patterns will be described in supplementary analyses.

All analyses will be performed using R (version 4.4.2). Statistical significance will be defined as a two-sided p-value < 0.05.

1. **Ethics and Confidentiality**

The study protocol will be reviewed and approved by the Institutional Review Board of Tsinghua University. All procedures will be conducted in accordance with the ethical standards of the Declaration of Helsinki and relevant national guidelines.

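### The primary outcome codes non-use of PrEP inconsistently: missing or non-adherent for event-driven users, adherent or non-adherent for daily users depending on how they read one item

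*Protocol*

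**What the plan says.** **ED users (section 3.6, Primary Outcome).** Participants with no sex in the window, and those who "reported to have never initiated PrEP in a previous question were treated as missing data for PrEP adherence", drop out of the outcome. The rest report how often they took PrEP at sexual encounters, with the options "1 = every time, 2 = sometimes, and 3 = never". Only those who took it every time and confirm all three dosing points are adherent; "otherwise, they would be classified as “non-adherent".

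**Daily users (same section).** "Adherence to daily PrEP regimen is assessed with a single item", which asks: "have you ever failed to take PrEP on time and in a correct dosage". *No* is adherent and *yes* is non-adherent. The daily paragraph does not mention initiation or current use.

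**Target.** The Primary Objective is "To evaluate medication adherence among real-world e-consumers of PrEP in China", and section 3.3 defines the study population as online purchasers. The inclusion criteria ask for a purchase and an intention to use PrEP over six months, not for a first dose. The Primary Outcome section, however, speaks of users of each regimen.

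**Missing data (section 3.8, Regression Analyses).** The analysis is complete-case without imputation, and "missing data are expected to arise primarily from loss to follow-up".

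**The concern.** Participants who took no pill in the same window can receive three different codes, depending on regimen, on whether they had ever started, and on how they read a negatively worded question. This is the primary outcome, and it feeds both the prevalence estimates and the regression models.

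Never-starters are a foreseeable group. The protocol writes a rule for them, eligibility does not require initiation, and section 3.4 allows recruitment at the moment of purchase.

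Two things are at stake. First, the ED and daily prevalences rest on different denominators, and a reader cannot tell whether either describes purchasers or people who have started. Second, initiation may depend on the factors under study, such as stigma, self-efficacy and depressive symptoms. The ED models are then conditional on initiation without saying so. The planned description of attrition would not reveal this, because these participants are still in follow-up.

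**Working it through.** **Step 1. The codes side by side.** Each participant below took no PrEP in the window.

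| Participant | Code under section 3.6 |
|---|---|
| ED, had sex, never initiated | missing |
| ED, had sex, initiated earlier, answers *never* | non-adherent |
| Daily, takes no pills, answers *no* to the item | adherent |
| Daily, takes no pills, answers *yes* to the item | non-adherent |

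**Step 2. Inputs.** Section 3.2 assumes 60% adherence and a 5-point margin of error. The never-initiated share *u* is not in the protocol; 5%, 10% and 20% are assumptions. So is *q*, the share of daily never-starters who answer *no*. Applying the 60% to initiators is a further assumption, since section 3.2 does not say to whom it refers.

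The 60% and the 5 points also produce the plan's sample size. With deff = 1 + (11 − 1) × 0.01 = 1.1 and N taken as 3,000 (N is not stated; this is the monthly sales figure in the rationale), Equation (1) gives 1.1 × 3,000 × 0.24 / [(0.0025/3.8416) × 2,999 + 0.24] = 361.4. Dividing by 0.85 gives 425.1, close to the stated 424. The present point does not depend on that number.

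**Step 3. ED users.** Adherence among all sexually active purchasers is 0.60 × (1 − u). The written rule reports 0.60 whatever *u* is, so the difference is 0.60 × u.

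| u (assumed) | Sexually active purchasers | Reported | Difference |
|---|---|---|---|
| 5% | 57% | 60% | 3 points |
| 10% | 54% | 60% | 6 points |
| 20% | 48% | 60% | 12 points |

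The difference passes the planned 5-point margin once u exceeds 0.05 / 0.60 = 8.3%. If the target is initiators, the reported 60% is the quantity wanted and the difference is zero.

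**Step 4. Daily users.** Reported adherence is 0.60 × (1 − u) + q × u. At u = 10%:

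| q (assumed) | Reported | Against purchasers (54%) | Against initiators (60%) |
|---|---|---|---|
| 0 | 54% | 0 | −6 points |
| 0.5 | 59% | +5 points | −1 point |
| 1 | 64% | +10 points | +4 points |

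Against purchasers, the error is zero or upward. Against initiators, it changes sign at q = 0.60.

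**Step 5. Missing data.** Section 3.8 names loss to follow-up as the main expected source. The ED rule adds two sources by definition, no sex and not started. The second is tied to non-use of the drug. Nothing in section 3.8 separates these from dropout.

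**The case against.** The strongest reply is that the ED rule is a deliberate definition. The Primary Outcome section is about regimen users; adherence is commonly kept apart from initiation, and a person who never started differs from one who lapsed. This stands: an initiators-only denominator is defensible, and under it the ED rule gives no bias. But the protocol does not state that target, its objective and study population point to purchasers, and the exclusion is written for one regimen only.

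A second reply is that the initiation item may be put to everyone. The protocol calls it only an earlier question, and section 3.7 mentions built-in logic constraints. This stands in part. A reader might infer that daily users are never asked about initiation; the text does not show that. It shows only that no rule applies the answer to them. Neither the general logic checks nor the pilot test in section 3.6 supplies such a rule.

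Third, a reader might infer that daily non-users are counted as adherent. The protocol does not establish this: someone taking no pills may well say they failed to take PrEP on time, and is then non-adherent.

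Fourth, section 3.8 says that missing data come primarily, not only, from dropout, and no figure in the protocol shows that expectation to be wrong. That is fair. The point is that the sources are not separated, not that the expectation is false.

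**Conclusion.** The inconsistency is on the face of the Primary Outcome section and remains under either target. Its effect depends on which target is meant:

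- **All purchasers:** ED adherence is overstated by 0.60 times the never-initiated share, if that share is above zero. Daily adherence is unaffected or overstated, depending on the answers given.
- **Initiators:** the ED rule is unbiased. Daily adherence can be too high or too low.

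A reader might conclude outright that adherence is overestimated by 3 to 12 points. The protocol does not support that: the size rests on assumed never-initiated shares and on 60% applying to initiators, and the direction is fixed only for ED users under a purchaser target. This is an inexpensive improvement to the outcome definition, worth making because it concerns the primary outcome.

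**What to change.** 1. State in section 3.6 whether adherence is meant for purchasers or for initiators.
2. Apply the ED initiation rule to daily users as well, and put a current-use question before the daily item, so that a daily initiator who took no PrEP in the past month cannot be scored adherent.
3. Report the never-initiated proportion by regimen and wave.
4. Keep the initiators-only analysis. Add a sensitivity analysis at the follow-up visits that counts sexually active ED never-initiators, and daily never-initiators, as non-adherent. Making this the primary coding is not advised: it would merge initiation with adherence. If baseline never-starters were left as not applicable, it would also change the outcome definition between baseline and follow-up, which Models 1 and 2 pool.
5. In section 3.8, separate values missing by definition (no sex, not started) from loss to follow-up.

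The cost is one routing question for daily users and a second reported adherence figure, which may be lower.

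### The adherence rules have no place for participants who started PrEP and then stopped because it was no longer indicated, and they treat event-driven and daily users differently

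*Protocol*

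**What the plan says.** **Entry.** The inclusion criteria in section 3.3 require a participant to be "Eligible for PrEP use according to national guidelines (e.g., HIV-negative, no contraindications to PrEP such as significant renal impairment", among other conditions. For the future they require only intent: "Planning to use PrEP over the next six months". Section 3.4 places the check at enrolment: "Investigators will verify inclusion/exclusion criteria, obtain informed consent, and finalize enrollment". No later check is described.

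**Follow-up.** Section 3.5 says "Follow-up assessments will occur at 1, 3, and 6 months after baseline", each visit being an online survey. On content, it says of the baseline form: "The questionnaire covers socio-demographics, PrEP regimen, adherence, psychosocial measures, and sexual behaviors". Sections 3.5 and 3.6 describe no item on current PrEP use, stopping or the reason for it. The secondary objectives name "willingness to use long-acting injectable PrEP, HIV testing behavior", but section 3.6 defines no item for these either.

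**Scoring of ED users (section 3.6, Primary Outcome).** Those with no sexual activity in the window, and those who "reported to have never initiated PrEP in a previous question were treated as missing data for PrEP adherence", leave the calculation. Everyone else is adherent only if PrEP was taken at every encounter and all three dosing questions are answered yes. All other answers, including never having taken it in the window, are non-adherent. Consistent adherence requires adherence over the past three months at both the 3- and the 6-month visit.

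**Scoring of daily users (same section).** They have the one item "In the past month, have you ever failed to take PrEP on time and in a correct dosage". No means adherent and yes means non-adherent. No exit is given, not even the never-initiated one.

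**Analysis (section 3.8).** These outcomes feed the mixed models and, for consistent adherence in ED users, a logistic model. The missing-data paragraph expects loss to follow-up to be the main source of gaps and does not mention participants who stopped PrEP.

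**The concern.** The ED rule already accepts that a person to whom adherence does not apply should not be scored: no sex and never started both go to missing. That principle is not carried through to participants who started and then stopped because PrEP was no longer indicated, and it is not applied to daily users at all. For these participants the primary outcome mixes failing to take an indicated medicine with no longer being a candidate for it.

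Two results are exposed. The first is the prevalence of adherence at each wave, which is reported by regimen. The second is the set of associations that the primary objective wants to use for interventions. Number of partners, chemsex and condom use are exposures in the models. If any of them goes with acquiring HIV, stops that follow a diagnosis could add to its apparent association with poor adherence.

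A later analysis plan could not repair this by itself. If the survey does not record the stop and its reason, there is nothing to reclassify on.

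**Working it through.** **Step 1. Apply the rules to each case.**

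| Participant's state in the recall window | ED user | Daily user |
|---|---|---|
| Never started PrEP | Missing | Scored: yes is non-adherent, no is adherent |
| Started, stopped as no longer indicated, no sex in window | Missing | Scored on the same item |
| Started, stopped as no longer indicated, had sex after the stop | Non-adherent: the answer is never, or sometimes if the stop fell inside the window | Scored on the same item |

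The third row is fixed for ED users, because either answer fails the every-encounter condition. It is not fixed for daily users. A person told to stop may answer yes, because doses were not taken, or no, because nothing that was due was missed. For consistent adherence in ED users, one such visit at 3 or 6 months is enough to fail the whole outcome.

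**Step 2. Confirm the planning values.** Section 3.2 gives p = 0.60, d = 0.05, a design effect of 1 + (11 − 1) × 0.01 = 1.1, and 15% loss. It does not state N. Taking N = 3,000 as an assumption from the monthly sales figure in section 1:

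- n = 1.1 × 3,000 × 0.24 / [(0.0025 / 3.8416) × 2,999 + 0.24] = 361.4
- 361.4 / 0.85 = 425.1, so 426.

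N = 2,900 gives 360.0 / 0.85 = 423.5, so 424, the stated figure. The sample size is not in dispute. The check only confirms 60% and 5 points as the yardstick.

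**Step 3. Size the misclassification.** Let f be the share of scored respondents in a regimen who stopped because PrEP was no longer indicated. The documents give no value for f, so every value below is an assumption. Let true adherence among the rest be 60%.

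- All such stoppers scored non-adherent: observed = 0.60 × (1 − f)
- All such stoppers scored adherent (possible for daily users only): observed = 0.60 × (1 − f) + f

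| f | All scored non-adherent | Shift (points) | All scored adherent | Shift (points) |
|---|---|---|---|---|
| 0.5% | 59.7% | −0.3 | 60.2% | +0.2 |
| 1% | 59.4% | −0.6 | 60.4% | +0.4 |
| 5% | 57.0% | −3.0 | 62.0% | +2.0 |
| 10% | 54.0% | −6.0 | 64.0% | +4.0 |

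The downward shift is 0.60 × f, so it reaches 5 points at f = 0.05 / 0.60 = 8.3%. If 60% is instead taken as the observed figure, the threshold is f = 1 − 0.60 / 0.65 = 7.7%.

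**The case against.** **The questionnaire is not shown.** Section 3.6 is not a complete item list. It refers to an earlier question on initiation that is described nowhere else, and the forms are still to be piloted and changed. This stands as far as it goes: silence does not prove that stopping goes unrecorded, and a reader should not infer that HIV status is certainly never asked about again. The scoring rules, however, are written out, and they would misclassify these participants whether or not an extra item exists.

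**Details of classification can be left to an analysis plan.** That would be a fair answer to a missing detail. Here the protocol states a rule that sends all remaining ED users to non-adherent, and a plan needs a recorded stop and reason to depart from it.

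**The effect may be trivial.** Only stops for an HIV diagnosis, a contraindication or clinician advice within six months count here. A share near 8% would be needed to match the planned margin. This stands, and it limits the weight of the point.

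**Stronger readings do not hold.** A reader might infer a general downward bias in adherence. The rules support that only for ED users who have sex after stopping; the daily item could err upward. A reader might also infer that comorbidity or HIV acquisition would emerge as predictors of poor adherence, but neither is among the measures in section 3.6. Lastly, a reader might infer that the study neglects safety risks it has itself named. The study is an observational survey of people who bought PrEP themselves, it assigns no treatment and has no safety objective, and HIV status and renal impairment appear only as examples under eligibility.

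**Conclusion.** The point holds as a gap in the primary outcome definition. The rules misclassify ED users who have sex after stopping PrEP that was no longer indicated. They give an uninterpretable score to daily users who stopped for the same reason or never started, and they allow exits in one regimen that the other lacks. The error is downward in the first group and undetermined in the second.

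The size cannot be derived from the documents. With 60% true adherence and all such stoppers scored non-adherent, the shift is 0.6 points at an assumed 1% and 3.0 points at an assumed 5%. The effect on prevalence may therefore be small. The effect on the associations cannot be sized either, since it depends on which exposures go with stopping. The change is worth making because it is cheap, and because without the items nobody can show that the effect was small.

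**What to change.** **Items.** At 1, 3 and 6 months, for both regimens and before the adherence questions, ask whether the participant has started PrEP, whether it is still in use and, if not, when and why it was stopped. List HIV diagnosis, contraindication and clinician advice separately from other reasons.

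**Scoring rule (section 3.6, Primary Outcome).**

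- Apply the never-initiated exit to daily users as well.
- Classify a person-visit as not applicable, outside the adherence denominator, if its recall window contains or follows a stop for HIV diagnosis, contraindication or clinician advice.
- Classify consistent adherence as not applicable if the 3- or the 6-month visit is affected.
- Keep stops for other reasons in the denominator, and state how a daily user in that group is scored, because the present item remains ambiguous for them.

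**Reporting (section 3.8).** Give the number in each category by wave and regimen, and repeat the analyses with the scoring as now written as a sensitivity analysis.

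The rule works on whole windows on purpose. The adherence items ask about a full month or three months, so time up to a stop cannot be scored separately without redesigning the recall. The change concerns classification only and sets no clinical rule on who should stop PrEP.

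**Cost.** A few more self-reported items, one of them sensitive, on forms that section 3.6 leaves open to change after piloting; a short addition to the outcome definition; and slightly fewer person-visits in the models, including some use before a stop within the same window.
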